# Effects of a multidisciplinary intervention to promote physical activity in patients with stroke undergoing rehabilitation: study protocol for the ActivePAS pilot randomised controlled trial

**DOI:** 10.1136/bmjsem-2022-001401

**Published:** 2022-10-25

**Keywords:** Physical activity, Health promotion, Rehabilitation, Intervention efficacy, Accelerometer

## Abstract

**Introduction:**

Physical activity after stroke is related to functional recovery and outcomes. To optimise physical activity adapted to a patient’s walking ability and characteristics, multidisciplinary support and interventions are required. The Activate Physical Activity for Stroke pilot randomised controlled trial aims to assess the safety and feasibility of a multidisciplinary intervention that promotes physical activity in patients who had a stroke undergoing rehabilitation.

**Methods and analysis:**

This single-centre, randomised controlled trial will enrol 32 patients who had a stroke undergoing rehabilitation. Patients who had a stroke with the ability to walk 50 m with at least hand assistance, regardless of the use of braces or walking aids, and aged≥20 years will be randomly allocated to a multidisciplinary intervention group or control group. Patients in the intervention group will receive instructions for the self-monitoring of hospitalised physical activity and support to promote physical activity by multidisciplinary staff. The primary outcome of the present study is the safety (adverse events) and feasibility (retention and completion rates) of the multidisciplinary intervention. We assess physical activity using a triaxial accelerometer (UW-204NFC, A&D Company) as one of the secondary outcomes.

**Ethics and dissemination:**

The present study has been approved by the Research Ethics Committee of Konan Women’s University and the Ethics Committee of Nishi-Kinen Port Island Rehabilitation Hospital. We will disseminate the results of the present study through a peer-reviewed manuscript and presentations at international conferences.

**Trial registration number:**

UMIN000046731.

WHAT IS ALREADY KNOWN ON THIS TOPICIn patients who had a stroke undergoing rehabilitation, promoting physical activity is positively associated with functional recovery and functional outcomes.However, the effectiveness of strategies to promote physical activity in patients who had a stroke undergoing rehabilitation has not yet been consistently reported, and thus, these strategies remain unestablished.WHAT THIS STUDY ADDSThe Activate Physical Activity for Stroke pilot randomised controlled trial will examine the safety and feasibility of a multidisciplinary intervention tailored to a patient’s individual characteristics that promotes physical activity in patients who had a stroke undergoing rehabilitation.The present study will include interventions based on comprehensive and multimodal instruction concepts, such as instructing the self-monitoring of physical activity, observing physical activity using multiperson monitor supporting, and encouraging physical activity by multidisciplinary staff.HOW THIS STUDY MIGHT AFFECT RESEARCH, PRACTICE OR POLICYThe results of the present study will provide preliminary data to test the efficacy of this intervention in a larger population.

## Introduction

Stroke is a leading cause of various and complex disabilities and mortality. Lower physical fitness due to poor cardiorespiratory fitness or muscle strength and other impairments, such as cognitive function and balance, interact to drive poststroke activity limitations.^1^ Activity limitations lead to a negative loop of lower physical activity and further declines in physical fitness.^1^ The promotion of physical activity and improvements in physical fitness may be needed to break this negative loop. However, patients who had a stroke tend to be inactive and sedentary during hospitalisation.^2–4^ This has been reported in both acute and rehabilitation hospitals.^5^ In patients who had a stroke undergoing rehabilitation, physical activity, such as daily step counts, wheelchair self-propulsion distance, and intensity-based physical activity, has been associated with mobility following discharge and functional recovery and outcomes during hospitalisation.^6–8^ Therefore, strategies to promote physical activity from the early stages of hospitalisation may need to be implemented regardless of stroke severity or gait independence.

Self-management is essential in patients who had a stroke to promote physical activity^9 10^ and prevent undesirable health issues.^10 11^ A systematic review has shown that self-management interventions using behaviour change techniques can potentially engage patients who had a stroke in physical activity for behavioural changes.^12^ Regarding self-management interventions, a theory of self-efficacy^13^ is important.^14^ The self-efficacy of a particular activity increases due to a self-management intervention.^15^ Self-efficacy has been reported to improve along with an increase in physical activity with accelerometer-based feedback in hospitalised patients who had a stroke.^16^ Behavioural change techniques, such as goal setting, feedback and encouragement from medical staff or family members, have also been used for patients who had a stroke as a strategy to promote physical activity.^16–19^ However, several randomised controlled trials to promote physical activity using accelerometers or pedometers in patients who had a stroke undergoing rehabilitation showed no efficacy.^17–19^ Therefore, it is of limited relevance to patients who had a stroke and is difficult to generalise. Although inclusion criteria (particularly walking ability) vary among studies,^17–19^ comprehensive or multimodal interventions may be necessary for populations that include patients with low walking ability after stroke.

Yamada *et al* reported that the number of steps taken outside of rehabilitation was associated with the activities of daily living (ADL) in patients who had a stroke undergoing rehabilitation who had a high ability to walk.^20^ Shimizu *et al* found a relationship between light-intensity physical activity, such as standing, stepping, slow walking and ADL, during hospitalisation and improved gait independence in patients who had a stroke who required assistance or supervision in walking.^8^ They also suggested the importance of effectively using the time outside of rehabilitation and not depending solely on time in rehabilitation to promote gait independence.^8^ On the other hand, a systematic review of qualitative studies showed that patients who had a stroke undergoing inpatient rehabilitation valued physical activity and expressed a desire to practice more outside rehabilitation.^21^ During the time outside of rehabilitation, a therapist’s attention is not focused on the patient; therefore, comprehensive interventions and support for physical activity by multidisciplinary staff may be necessary. Furthermore, since this support and interventions are recommended to be personalised and multimodal,^22^ the walking ability and self-efficacy of a patient need to be considered. Therefore, we hypothesised that a multidisciplinary intervention tailored to a patient’s individual characteristics would effectively promote physical activity in patients who had a stroke undergoing rehabilitation.

### Objectives

The objective of the present study is to describe the study protocol for ‘a multidisciplinary intervention to Activate Physical Activity for Stroke—ActivePAS’. The primary objective of the ActivePAS pilot randomised controlled trial is to examine the safety and feasibility of the multidisciplinary intervention that promotes physical activity in patients who had a stroke undergoing rehabilitation. In addition, the present trial will assess the effects of a multidisciplinary intervention that promotes physical activity in these patients.

## Methods and analysis

This protocol is reported following Standard Protocol Items: Recommendations for Interventional Trials 2013 guidelines for clinical trial protocols.^23^

### Trial design

This study is a single-centre, prospective, open-label, randomised controlled trial. An independent researcher not involved in enrolment or outcome measurements performed randomisation using a computer-generated 1:1 allocation sequence and permuted block size of 4. The flow chart of the present study is shown in figure 1.

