### Eligibility criteria

The inclusion and exclusion criteria for the present study are shown in box 1. Two or more physical therapists or physicians will assess patients’ eligibility to participate in the present study. We will include patients hospitalised for stroke with the ability to walk 50 m with at least hand assistance, regardless of the use of braces or walking aids, and aged ≥20 years. If a patient does not meet the above criteria at the time of admission, they will still be included in the present study if they can walk during hospitalisation. All patients will obtain informed consent before inclusion and randomisation (table 1).

Box 1Inclusion and exclusion criteria of the present studyInclusion criteriaPatients hospitalised for strokePatients with the ability to walk 50 m with at least hand assistanceAge≥20 yearsExclusion criteriaSAHStroke after cardiovascular surgeryPremorbid mRS≥3Cognitive impairment (MMSE score<21)^33^Patients who are expected to be hospitalised for less than 2 weeksPatients who have neurological, orthopaedic, or medical diseases other than stroke that seriously affect physical activityPatients who cannot give consent for research participation.MMSE, Mini-Mental State Examination; mRS, modified Rankin Scale; SAH, subarachnoid haemorrhage.

**Table 1 T1:** Summary of the study schedule

Time point	Study period			
	Baseline	Allocation	Intervention	
			Week 1	Week 4
Enrolment				
Demographic data	×			
Informed consent	×			
Allocation		×		
Interventions				
Intervention group				
Conventional rehabilitation	×		×	×
Multidisciplinary intervention			×	×
Self-monitoring of PA			×	×
Control group				
Conventional rehabilitation	×		×	×
Assessment				
Stroke severity				
NIHSS	×			
Motor dysfunction				
FMA-LE	×			
Safety			×	×
Feasibility	×		×	×
PA			×	×
Physical function				
Walking speed	×			×
SPPB	×			×
6MWD				×
Functional outcome				
FIM-M	×			×
Self-efficacy for PA	×			×

FIM-M, Functional Independence Measure for motor function; FMA-LE, Fugl-Meyer Assessment for lower extremity; 6MWD, 6-minute walking distance; NIHSS, National Institutes of Health Stroke Scale; PA, physical activity; SPPB, Short Physical Performance Battery.

The present study was registered at the University Hospital Medical Information Network Clinical Trial Registration before the enrolment of patients (ID: UMIN000046731). A flow chart of participants will be reported according to the Consolidated Standards of Reporting Trials guidelines (figure 1).

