### Randomisation and blinding

Study enrolment will be implemented at a single convalescent hospital in Japan. Permuted block randomisation will be used, with a computerised random allocation sequence generated by an independent researcher throughout the study to facilitate data management. Randomisation is stratified by the ability or inability to walk independently. An answer form will be sent to the investigators, including a randomisation number.

Allocation results are disclosed to trial participants, outcome assessors and medical staff. Allocation results are not disclosed to the data analyst. To ensure that the statistical analysis is blind, the data analyst’s intervention/control group codes are masked until the data analysis is complete.

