FIM is one of the most common measurement tools for ADL.^26^ FIM-M has 13 subitems, and tasks are rated on a seven-point ordinal scale that ranges from requiring total assistance to complete independence. Walk subitem scores of FIM-M at baseline will be used for the allocation described above. Specifically, we stratify patients with walk subitems scores of 6 (modified independence) and 7 (complete independence) as the ability to walk, and those with scores of 4 (minimal assistance) and 5 (supervision) as an inability to walk. Physical or occupational therapists evaluate the functional status of all patients using this tool as part of the rehabilitation protocol during hospitalisation.

SEPA is measured with the Japanese version of the SEPA scale with validated reliability.^27^ This assessment was developed based on the study by Ewart *et al*.^28^ The measure consists of the following four subscales: the domain of walking, stair climbing, weight lifting and push-off, and subjects are asked to answer the degree of confidence for the activity load class. In the present study, we will use the walking domain as the SEPA index. SEPA scores range between 0 and 100, with lower scores indicating a poor level of SEPA and higher scores indicating a better level of SEPA.

We will assess baseline neurological deficits and motor dysfunctions as adjustment factors in statistical analysis. The former will be assessed by the National Institutes of Health Stroke Scale (NIHSS)^29^ and the latter by the Fugl-Meyer Assessment for lower extremity (FMA-LE).^30^ NIHSS is scored from 0 to 42 points, with higher scores indicating more severe symptoms. FMA-LE is scored from 0 (hemiplegia) to a maximum of 34 points. Seventeen items are included in lower limb FMA, and each item is scored on a three-point ordinal scale (zero=cannot perform, one=performs partially, and two=performs fully).

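### A single stated block size of 4 in an open-label, single-centre trial lets staff who track each walking stratum know up to about one third of assignments in advance

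*Protocol article*

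**What the plan says.** The Trial design section of the protocol article states: "This study is a single-centre, prospective, open-label, randomised controlled trial". It adds that an independent researcher, outside recruitment and measurement, "performed randomisation using a computer-generated 1:1 allocation sequence and permuted block size of 4".

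The Randomisation and blinding section gives the rest of the mechanism:
- On who learns the assignment once it is made: "Allocation results are disclosed to trial participants, outcome assessors and medical staff".
- On the strata used for the lists: "Randomisation is stratified by the ability or inability to walk independently".
- On how the hospital receives each result from the holder of the list: "An answer form will be sent to the investigators, including a randomisation number".

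That section mentions permuted blocks again. It does not say that block sizes vary or that the size is withheld from the hospital.

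The Secondary outcomes section explains how strata are assigned: "Walk subitem scores of FIM-M at baseline will be used for the allocation described above". Scores of 6 and 7 form one stratum, and scores of 4 and 5 the other.

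On who decides entry, the Eligibility criteria section says: "Two or more physical therapists or physicians will assess patients’ eligibility to participate in the present study". Of patients who do not qualify on admission it says that "they will still be included in the present study if they can walk during hospitalisation".

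**The concern.** Having an outsider hold the list conceals it only if the next entry cannot be deduced from earlier ones. With a constant block of 4, once one arm has filled its two places the rest of the block is determined. The history needed for that deduction is open to medical staff, and the stratum of a candidate is known from a score that therapists record.

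The same professions screen candidates. Most criteria are objective, but two leave room for judgement: whether the stay is likely to be shorter than two weeks, and whether another disease limits activity seriously enough to exclude. Someone who expected a given arm could, even without intending to, read those criteria more strictly or more loosely.

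At stake is comparability of the arms for steps, physical function and adverse events such as falls. The planned adjustment would not restore it fully. The model for steps uses age, sex, NIHSS and FMA-LE, and Table 1 schedules neither physical activity nor 6-minute walking distance at baseline.

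**Working it through.** The article gives no predictability figure, so there is none to reproduce.

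**Inputs.** Block size 4 and ratio 1:1 (Trial design); two strata (Randomisation and blinding; Secondary outcomes); target of 32 patients (Statistical analysis and sample size). Assumption: the observer knows the block size and the order of past allocations within each stratum.

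**Certain assignments per block.** There are 4!/(2!2!) = 6 equally likely orders. An assignment is certain when one arm already has two places.
- Positions 1 and 2: probability 0.
- Position 3: the first two must be alike, 2/6 = 1/3.
- Position 4: probability 1.

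Sum: 4/3 per block, and (4/3)/4 = 33.3%.

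**Best-guess success**, naming the arm that is behind and tossing a coin when tied.
- Position 1: 1/2.
- Position 2: 2/3.
- Position 3: 1/3 × 1 + 2/3 × 1/2 = 2/3.
- Position 4: 1.

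Mean: (1/2 + 2/3 + 2/3 + 1)/4 = 70.8%.

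**Over 32 patients in two strata.** The split between strata is unknown, so the result depends on the incomplete last blocks.
- Both strata multiples of 4: 8 × 4/3 = 10.7 (33.3%).
- One patient over in one stratum and three in the other: 7 × 4/3 + 0 + 1/3 = 9.7 (30.2%).
- Two over in each: 7 × 4/3 + 0 + 0 = 9.3 (29.2%).

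Best-guess success is 70.8% in the first case. In the other two it is (7 × 17/6 + 7/3)/32 = 69.3%.

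**Varying block sizes.** Simulation, 4,000 runs, sizes equally likely, observer assumed to know the set of sizes and all past allocations. Main figures are for a sequence of 32; figures in brackets are for a stratum of 16.

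| Block sizes | Certain | Best guess correct |
|---|---|---|
| 4 only (exact) | 33.3% | 70.8% |
| 2 and 4 | 10.7% (10.4%) | 72.0% (71.7%) |
| 4 and 6 | 5.8% (6.0%) | 68.8% (68.4%) |
| 2, 4 and 6 | 4.0% (3.8%) | 69.8% (69.4%) |
| 4, 6 and 8 | 2.2% (2.3%) | 67.5% (66.9%) |

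With sizes 4 and 6, certain assignments fall to about 0.058 × 32 = 1.8 patients. Varying the size removes most of the certainty but little of the guessing advantage. The choice of sizes matters: 2 and 4 together does clearly worse than the other sets.

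**The case against.** The strongest reply has four parts.

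**Safeguards exist.** An independent researcher generates the sequence, at least two clinicians judge eligibility, most criteria are objective, consent precedes randomisation, and Table 1 puts baseline before allocation. All of this stands and narrows the opening. It does not close it, because the assessors belong to the staff groups to whom past allocations are disclosed.

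**The consequences are limited.** The primary outcome is safety and feasibility, and the secondary outcomes are labelled exploratory. Stratification on independent walking, and the covariates in the model for steps, absorb part of any selection on walking ability. This also stands. A reader might infer that the feasibility results are undermined. The article does not support that, since retention and completion depend much less on who enters which arm. The comparison of adverse events remains exposed.

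**Discretion over timing is not shown.** A reader might infer that staff can pick the enrolment date to suit the next assignment. The article allows later entry once a patient can walk, but it does not say who sets the date or that the date is discretionary. That step should not be asserted.

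**The contrast with 50% flatters the remedy.** A 50% guessing rate belongs to simple randomisation, which is not what is proposed. The simulation confirms that varying block sizes leaves the rate at about 67% to 70%. The case for the change rests on removing certain foreknowledge.

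**Conclusion.** The point holds as a design vulnerability. With a constant block of 4, an observer who tracks both strata could be certain of 9.3 to 10.7 of 32 assignments (29% to 33%). This rests on three assumptions: the observer knows the size, knows the order of past allocations within each stratum, and the trial reaches 32 patients. If tracking is imperfect, the figure is lower.

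The effect would fall on the between-group comparisons of steps, function and adverse events, with stratification and covariate adjustment offsetting only part of it for steps.

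A reader might go further and infer that prediction took place, or that printing the block size in the article caused the exposure. Neither is supported. The article gives no sign that anyone used such knowledge, and it does not say whether recruitment was still open when it appeared. Its limitations paragraph acknowledges possible bias because many staff will know the groups, but it does not address prediction before entry. For a pilot this is a cheap improvement and does not invalidate the design.

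**What to change.** For any patients not yet randomised:

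1. Have the independent researcher generate a new sequence within each walking stratum, using randomly varying block sizes (for example 4 and 6), and disclose neither the sizes nor the set to hospital staff.
2. Release each assignment only after eligibility, consent and baseline data have been registered irrevocably. Consent and baseline before allocation are already planned, so only the irrevocable registration is new.
3. State what happens to blocks of 4 that are part-filled at the switch. Completing them leaves their last places predictable; abandoning them can add a difference of up to 2 patients per stratum.

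The cost is a new list, one registration step and slightly looser balance. An unfinished block can leave a difference of at most half its size. With two strata the worst case is 2 × 2 = 4 patients with blocks of 4 (18 against 14 of 32), and 2 × 3 = 6 with blocks up to 6 (19 against 13), before any abandoned blocks.

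If recruitment is complete, report the predictability as a limitation and show baseline balance by arm within each walking stratum.

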**Figure 1 F1:**
[figure not shown]
Study flow diagram.

### Study setting

This study will be conducted in a single convalescent hospital in Japan.

### Eligibility criteria

The inclusion and exclusion criteria for the present study are shown in box 1. Two or more physical therapists or physicians will assess patients’ eligibility to participate in the present study. We will include patients hospitalised for stroke with the ability to walk 50 m with at least hand assistance, regardless of the use of braces or walking aids, and aged ≥20 years. If a patient does not meet the above criteria at the time of admission, they will still be included in the present study if they can walk during hospitalisation. All patients will obtain informed consent before inclusion and randomisation (table 1).

Box 1Inclusion and exclusion criteria of the present studyInclusion criteriaPatients hospitalised for strokePatients with the ability to walk 50 m with at least hand assistanceAge≥20 yearsExclusion criteriaSAHStroke after cardiovascular surgeryPremorbid mRS≥3Cognitive impairment (MMSE score<21)^33^Patients who are expected to be hospitalised for less than 2 weeksPatients who have neurological, orthopaedic, or medical diseases other than stroke that seriously affect physical activityPatients who cannot give consent for research participation.MMSE, Mini-Mental State Examination; mRS, modified Rankin Scale; SAH, subarachnoid haemorrhage.

**Table 1 T1:** Summary of the study schedule

Time point	Study period			
	Baseline	Allocation	Intervention	
			Week 1	Week 4
Enrolment				
Demographic data	×			
Informed consent	×			
Allocation		×		
Interventions				
Intervention group				
Conventional rehabilitation	×		×	×
Multidisciplinary intervention			×	×
Self-monitoring of PA			×	×
Control group				
Conventional rehabilitation	×		×	×
Assessment				
Stroke severity				
NIHSS	×			
Motor dysfunction				
FMA-LE	×			
Safety			×	×
Feasibility	×		×	×
PA			×	×
Physical function				
Walking speed	×			×
SPPB	×			×
6MWD				×
Functional outcome				
FIM-M	×			×
Self-efficacy for PA	×			×

FIM-M, Functional Independence Measure for motor function; FMA-LE, Fugl-Meyer Assessment for lower extremity; 6MWD, 6-minute walking distance; NIHSS, National Institutes of Health Stroke Scale; PA, physical activity; SPPB, Short Physical Performance Battery.

The present study was registered at the University Hospital Medical Information Network Clinical Trial Registration before the enrolment of patients (ID: UMIN000046731). A flow chart of participants will be reported according to the Consolidated Standards of Reporting Trials guidelines (figure 1).

